# Blinding

Blinding is not applicable to this study. Due to the nature of the intervention it is not possible for the intervention delivery team or midwives to be blinded. However, aspects of the study where some degree of blinding will be utilised including:

- The NHS Trusts will be given a unique ID code and the statistician performing the randomisation will be blind to the NHS Trusts during the process of cluster randomisation
- The midwives and pregnant women will be given a unique ID code and the statistician performing the randomisation will be blind to the participant details during the process of random selection of midwives and women
- The pregnant women involved in the study will not be informed by the researchers whether their midwives are in the intervention or control arm of the study, and midwives will be asked not to disclose this information to women during their consultations
- Midwives will not be aware which arm of the trial their NHS Trust has been allocated to when consenting and providing baseline data

# Study Data

In addition to the data required to meet the aims of the pilot study (detailed in section 9), one of the purposes of the pilot study is to determine which outcome to use as the primary outcome and which should be secondary in a definitive trial. The proposed primary and secondary outcomes will be collected during the pilot study in line with the primary and secondary aims of the intervention.

- Primary aim: midwives behaviours
- Primary outcome: change in midwives clinical practice
- Potential primary outcome measures:
  - Midwives self-reported practice
  - Women’s self-report of their midwives practice
  - Case note audit of recorded midwifery practice
  - Vignettes of different types of consultation (simulated practice)
- Secondary aim: women’s weight and weight-related behaviours
- Primary outcome: change in weight from booking
- Potential primary outcome measures:
  - Pregnancy weight: 3^rd^ trimester,
  - Postnatal weight: 3, 6, 9, 12 months
- Secondary outcomes: 3^rd^ trimester and 3, 6, 9, 12 months postnatal
  - Dietary behaviours
  - Physical activity behaviours
  - Psychosocial measures for weight-related behaviours
  - Therapeutic alliance with midwives (3^rd^ trimester of pregnancy only)
  - Quality of life

All primary data collection will be anonymised using the participant’s unique study ID number. An overview of the study data are presented in table 2.

Table 2. Data collection type, populations, sites, time points, and consent

|  | **Baseline (pre-intervention)** | **Intervention delivery** | **1 month post intervention** | **3 months following intervention delivery (to all midwives)** | **6 months following intervention delivery (to all midwives)** | **3 months postnatal** | **6 months postnatal** | **9 months postnatal** | **12 months postnatal** |
| --- | --- | --- | --- | --- | --- | --- | --- | --- | --- |
| **Maternity electronic patient records (all clusters)** | Eligible pregnant women’s characteristics |  |  |  |  |  |  |  |  |
| **Random sample of 18 women attending 20 week scan/ cluster (all clusters)** | Consent, women's characteristics, questionnaire data.  Case note audit (economic evaluation phase 1) |  |  |  |  |  |  |  |  |
| **Random sample of 18 midwives/ cluster (all clusters)** | Consent, midwives characteristics, questionnaire data |  |  | Questionnaire data | Questionnaire data |  |  |  |  |
| **All community midwives/cluster (intervention arm, 2 clusters)** |  | Consent, intervention delivery, completion of evaluation forms |  |  |  |  |  |  |  |
| **Random sample of 7 midwives/ cluster (intervention arm, 2 clusters)** |  |  | Consent, focus groups |  |  |  |  |  |  |
| **Convenience sample of 30 women/ cluster (all clusters)** |  |  |  |  | Consent women at 12 week scan and questionnaire data; follow up at 36 weeks, questionnaire data and weight measurement | Questionnaire data, weight measurement, case note audit | Questionnaire data, weight measurement | Questionnaire data, weight measurement | Questionnaire data, weight measurement |
| **Convenience sample of 10 recruited women/cluster (all clusters)** |  |  |  |  | Consent at 12 weeks, semi-structured interviews (3rd trimester) |  | Semi-structured interviews |  |  |

Study data collection details:

- Maternity electronic patient records: pregnant women’s characteristics including maternal age, BMI, ethnic group, parity, employment status, socio-economic status (determined by postcode anonymised by data linkage with index of multiple derivation data) will be retrieved from the electronic patient records for all eligible women in their 3^rd^ trimester during the recruitment period. Data will be anonymised and aggregated to compare with recruited women to determine any participation bias for each site.
- Women at 20 week scan – baseline only: eligible women will be approached and consented by a member of the research team (as per delegation log) before the intervention delivery to provide baseline data on their characteristics (including maternal age, gestation, BMI, ethnic group, parity, employment status, qualifications, postcode), questionnaire data. This is a one off data collection to compare how similar women are within and between sites before the midwives caring for them have received any intervention. The questionnaire data are:
  - Self-report of their midwives practice specific to the guideline recommendations (developed to reflect the midwives self-reported routine practice behaviour measurements)
  - Dietary Quality Score (DQS – validated in non-pregnancy with additional pregnancy and postnatal specific questions included)
  - Pregnancy Physical Activity Questionnaire (PPAQ – validated in pregnancy)
  - Psychosocial measures for understanding weight-related behaviours in pregnant women questionnaire (validated in pregnancy)
  - Therapeutic alliance with midwives (Health Care Alliance Questionnaire - validated in pregnancy)
  - Quality of life (EQ5D 5L)
- Case note audit to inform economic evaluation: the medical records of women consenting to provide baseline data prior to intervention delivery to inform the data collection requirements for economic evaluation (phase 1 as detailed in section 9.1.3).
- Midwives: Midwives will be consented at baseline, and asked to complete a form with their characteristics (number of years practice, speciality, ethnic group, age, and gender), and questionnaire data. The questionnaire data collection will be repeated at two further time points post-intervention. The questionnaire will include:
  - Self-reported routine practice specific to the guideline recommendations (current weight communication and weight management clinical practice/behaviours)
  - SCT constructs: self-efficacy, outcome expectancies, goals/intentions (weight communication and weight management specific),
  - Additional constructs identified in the SCT model: knowledge of the guideline recommendations and attitudes towards obese populations
  - Vignettes of different types of consultations (based on the type of consultations midwives report as challenging in the existing evidence-base)
- Eligible midwives in the intervention arm: Midwives will be consented to receive the intervention (including observations and video recording), and will be asked to complete intervention evaluation forms
- Eligible midwives in the intervention arm: Midwives in the intervention arm will be consented to participate in focus groups as part of the process evaluation
- Eligible women at 12 week scan appointment: eligible women will be approached and consented to provide data on their characteristics (including maternal age, gestation, BMI, ethnic group, parity, employment status, postcode), questionnaire data, and 3^rd^ trimester weight measurements (to calculate weight change from booking). Some of the questionnaire data and weight measurements will be repeated postnatally (see table 2 for details of pregnancy and postnatal specific data collection). Recruited and consenting women’s case notes will be audited to determine feasibility of using this data source to inform the primary outcome, and to test the data collection form developed for the economic evaluation (phase 2 detailed in section 9.1.3). Case notes are retained by pregnant women antenatally and returned to the NHS Trust after discharge; therefore the audit will take place 3 months postnatally when case notes are returned.
- A subgroup of eligible women recruited to provide outcome data: women will be approached and consented by a member of the research team (as per delegation log) to take part in semi-structured interviews as part of the process evaluation. Interviews will take place during their last trimester of pregnancy, and again postnatally.

# Statistical & Analytical Considerations

All quantitative and qualitative data analysis will be descriptive with the purpose of informing the development of the definitive trial. Analysis will include fidelity of intervention delivery (i.e. have all components of the intervention been delivered as planned), any intervention organisation and delivery requirements, data collection procedures for a definitive trial, data requirements, timescale and procedures for data manipulation for a definitive trial.

Thematic analysis will be used for the qualitative data (by the CI and Project Research Midwife). The analyses will be used to inform the further development and refinement of the intervention content, delivery, and data collection procedures and tools prior to a definitive trial.

16.1 Statistical Analysis Methods

The data analysis of the outcome measures will be descriptive (percentages, means and standard deviations or 5-number summaries as appropriate), with the primary aim of providing estimates of key trial parameters, including rates of recruitment, retention, data completion, and the variability of proposed outcome measures. These key trial parameters will be used to inform power calculations for the definitive trial (see section 9.1.3), and to inform decisions about which outcome measures to use in the definitive trial (e.g. are any time points for maternal weight status consistently complete/incomplete, what data we can yield from the case note audit etc). Analyses required to inform power calculations for a definitive trial are:

- An estimate of the variability (standard deviation) for those in the control group for continuous outcomes measures
- An estimate of proportions (percentages) for categorical outcome measures
- An estimate of the intra cluster correlation (ICC) for these measures to inform the power calculation, though given the imprecision in this estimate, due to the small sample size, other sources of estimates will need to be explored.

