# Objectives

The aim of a definitive evaluation of the proposed intervention would be to address the following research questions:

1. Does a theory-based intervention facilitate the implementation of weight management guidelines into midwifery practice?
2. Does midwifery implementation of weight management guidelines mediate obese pregnant and postnatal women’s weight and weight-related behaviours?

The primary outcome for this type of implementation intervention would relate to measures of health professionals’ practice. Secondary outcome measures would relate to measures of women’s weight status and weight-related behaviours. Such an evaluation would require a large-scale cluster RCT. Large scale evaluations of interventions can be limited by poor recruitment and retention rates, limited acceptability of and compliance with the intervention (by those delivering and receiving it), and process issues in the intervention delivery [[48](#_ENREF_48)]. The MRC stresses the importance of conducting pilot studies prior to large scale trials when the intervention has multiple components [[48](#_ENREF_48)]. Pilot studies can explore such potential issues to inform the design and conduct of a definitive study [[49](#_ENREF_49) [50](#_ENREF_50)]. Therefore a necessary prerequisite, and the focus of this study, is a pilot study to ensure methodological rigour, scientific validity, and inform the development of a protocol for that definitive trial [[49](#_ENREF_49)]. A rehearsal pilot trial of the intervention will be carried out, with integrated process evaluation. A key priority for assessment of complex interventions includes identifying how it works in everyday practice, which will be achieved through the process evaluation element of the rehearsal pilot trial [[48](#_ENREF_48)]. The aim of the proposed multi-centre rehearsal pilot cluster RCT is:

- To pilot a theory-based intervention to facilitate the implementation of weight management guidelines into midwifery practice

The specific pilot study objectives are to:

1. Pilot the intervention delivery, data collection and analysis methods to assess feasibility and acceptability thereof
2. Explore the intervention’s active ingredients (in success or failure) through process evaluation
3. Collect baseline and outcome data required to inform sample size estimations and scope data collection procedures for economic evaluation within the definitive trial

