16.2 Pilot Study Sample Size

Sample sizes for pilot studies are typically not informed by formal power calculations, but rather by pragmatism and resource constraints; it has been proposed that outcome data from approximately 30 participants per arm is adequate [[49](#_ENREF_49) [50](#_ENREF_50)]. Four clusters (NHS Trust maternity services) will be studied; two per arm.

All community midwives in intervention arm units will be targeted to receive the intervention, as shared midwifery care requires all midwives within the team to be consistent in their provision of care to this population. The aim is to obtain outcome data from 30 midwives and 30 pregnant women in each arm (15/cluster). In each cluster we will aim to recruit 18 midwives, 18 pregnant women (baseline), and 30 pregnant women (post-intervention follow up) to provide outcome data for statistical analysis in the pilot trial, to allow for withdrawal and loss to follow up. The aim is to obtain qualitative process evaluation data from 5 midwives in each NHS Trust in the intervention arm, and 5 pregnant women from each participating NHS Trust. We will aim to recruit 7 midwives and 10 pregnant women from each of the relevant pilot sites to allow for withdrawal and loss to follow up.

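### For midwife-reported measures, the planning SD could draw on all four Trusts and the baseline-to-follow-up correlation could be added, at no cost in data

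*Protocol*

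**What the plan says.** Objective 3 of the pilot (protocol, Objectives) is to "Collect baseline and outcome data required to inform sample size estimations" for the definitive trial. Section 16.1 turns this into a list introduced by "Analyses required to inform power calculations for a definitive trial are". The list has three items:

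- for continuous outcomes, "An estimate of the variability (standard deviation) for those in the control group for continuous outcomes measures";
- proportions for categorical outcomes, with no arm named;
- "An estimate of the intra cluster correlation (ICC) for these measures to inform the power calculation", with the caveat that this estimate will be imprecise and that other sources will have to be explored.

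No reason is given for limiting the SD to the control group, and no correlation over time is listed. The opening of the same section states a wider aim, "and the variability of proposed outcome measures", which is not tied to one arm.

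On design, section 16.2 says: "Four clusters (NHS Trust maternity services) will be studied; two per arm". It targets outcome data from 15 midwives per cluster, with 18 recruited. Section 13.1 places midwife consent and baseline data before randomisation. Table 2 and the text below it (Study Data) show the random midwife sample in all clusters completing the questionnaire at baseline and at two later time points. The questionnaire covers self-reported practice, the Social Cognitive Theory constructs and the vignettes. The main midwife outcome is framed as change: "Primary outcome: change in midwives clinical practice".

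**The concern.** Sample-size inputs are one of the pilot's three products. The listed SD uses one of two equal arms, while the midwife data offer two further sources. One is a pre-randomisation measurement in all four Trusts, which no intervention effect can have touched. The other is follow-up in the intervention arm. A planning SD enters the sample size as its square, so imprecision in the SD is magnified in the number of participants.

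The same midwives are measured three times. If the definitive trial adjusts for baseline, the correlation between baseline and follow-up is a direct input to its size, and for these measures the pilot could estimate it. An unadjusted follow-up SD used for a baseline-adjusted analysis would oversize the trial.

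**Working it through.** **The plan's own figures.** 15 per cluster × 2 clusters = 30 midwives per arm; × 4 clusters = 60 in all. Recruiting 18 to obtain 15 allows for 1 − 15/18 = 16.7% loss. Both agree with section 16.2. The protocol gives no alpha, power or effect size for the definitive trial, so its sample size cannot be reproduced. Everything below is a multiplier on whatever size is planned.

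**Precision of the SD.** The 95% limits for the true variance, relative to the estimate, are df/χ²(0.975, df) and df/χ²(0.025, df). The SD limits are their square roots. Sample size is proportional to the variance. With degrees of freedom taken within cluster:

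| Source | df | Limits on planned N | Limits on SD |
|---|---|---|---|
| Control arm only, 30 midwives in 2 Trusts | 30 − 2 = 28 | 28/44.46 = 0.63 to 28/15.31 = 1.83 | 0.79 to 1.35 |
| All four Trusts, 60 midwives | 60 − 4 = 56 | 56/78.57 = 0.71 to 56/37.21 = 1.50 | 0.84 to 1.23 |

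The SD interval narrows from 0.559 to 0.382, about 32%. The upper limit on N falls by 1 − 1.505/1.829 = 18%. If all 72 recruited midwives supply baseline data (72 − 4 = 68 df), the limits on N are 0.73 to 1.44.

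These intervals ignore clustering. The 56 df row applies to follow-up only if training leaves the variance unchanged. For the pre-randomisation data that assumption concerns only similarity across untreated Trusts, but the result is then a baseline SD.

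**Between-Trust variance.** Two control Trusts give 2 − 1 = 1 df. Four Trusts at baseline give 4 − 1 = 3. Four Trusts at follow-up with arm fitted give 4 − 2 = 2. More Trusts help, but no option estimates the ICC well.

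**Value of the correlation.** With baseline adjustment, the individual-level variance is multiplied by 1 − r². The protocol states no r, so the values are assumptions:

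| Assumed r | 1 − r² | Overstatement of N if r is ignored, 1/(1 − r²) |
|---|---|---|
| 0.3 | 0.91 | 1.10 |
| 0.5 | 0.75 | 1.33 |
| 0.7 | 0.51 | 1.96 |

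**Precision of the correlation.** By Fisher's z, at r = 0.5 the transformed value is 0.549 and the half-width is 1.96/√(n − 3). With n = 30 the half-width is 0.377, giving 0.17 to 0.73. With n = 60 it is 0.260, giving 0.28 to 0.67.

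**Where the correlation exists.** Study Data names four candidate primary measures of midwife practice. Midwife self-report and vignettes are repeated in the same midwives. Women's reports are not measured before and after in the same women: the 20-week baseline sample is a one-off, and the follow-up women are recruited after the training. The case-note audit used for outcome likewise has no paired pre-intervention record.

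**The case against.** A control-only SD is common practice. Training may widen or narrow the spread of self-reported practice, and pooling arms at follow-up assumes it does not. The pre-randomisation SD avoids that assumption but is not a follow-up SD. This stands: the gain is in precision, and no error is corrected.

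It can also be said that confidence intervals and a model term for arm belong in an analysis plan. That is fair for those details. But section 16.1 itself fixes the SD source and lists the required inputs, so a suggestion on those two items is in place.

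The gain is also modest. At a one-sided 80% upper limit, planned N would be 1.30 times the estimate with 28 df and 1.19 with 56 df, a difference of about 8%. And if the outcome is analysed as change, the SD of change already contains the correlation, so listing it separately matters mainly for a baseline-adjusted analysis of follow-up scores.

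A reader might infer three stronger things, and the protocol supports none of them:

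- **That half or more of the data is thrown away, against objective 3.** Control follow-up is indeed 30 of 60 midwives. But section 16.1 does not bar other SDs, its opening aim names no arm, and the control-group item does not say follow-up only. Objective 3 says only that baseline and outcome data will be collected to inform sample size.
- **That the ICC will be inflated by the training effect, or will rest on two control Trusts.** The ICC item states neither rule, and it already concedes imprecision and points to other sources.
- **That the definitive trial will therefore be wrongly sized.** Section 9.1.3 leaves the sample size to the trial statistician, and section 16.1 expects ICC estimates from elsewhere.

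**Conclusion.** The point holds as a free improvement. For midwife-reported measures, the protocol names a less precise planning SD than its data can provide and omits a correlation that the same data would supply. The range of uncertainty on planned N is 0.63 to 1.83 times the estimate with control-only data and 0.71 to 1.50 times with four Trusts, ignoring clustering, at the planned 15 midwives per Trust and with equal variances. If the definitive trial adjusts for baseline, the correlation could reduce the individual-level variance by 9%, 25% or 49% at assumed r of 0.3, 0.5 or 0.7. The point does not extend to women's reports or the case-note audit, and the ICC remains the larger uncertainty whichever data are used.

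**What to change.** In section 16.1, for midwife-reported measures only (self-reported practice, vignettes, Social Cognitive Theory constructs), keep the control-group SD and add:

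- the pre-randomisation SD and ICC from all four Trusts;
- the follow-up SD and ICC pooled within arm, with arm as a fixed effect, and a note that this assumes equal variances in the two arms;
- the baseline-to-follow-up correlation.

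Report each with a confidence interval. Leave the statement on outside ICC sources as it is. The cost is a few lines of text and analysis code, with no new data and no added burden on participants.

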16.2 Pilot Study Sample Size

Sample sizes for pilot studies are typically not informed by formal power calculations, but rather by pragmatism and resource constraints; it has been proposed that outcome data from approximately 30 participants per arm is adequate [[49](#_ENREF_49) [50](#_ENREF_50)]. Four clusters (NHS Trust maternity services) will be studied; two per arm.

All community midwives in intervention arm units will be targeted to receive the intervention, as shared midwifery care requires all midwives within the team to be consistent in their provision of care to this population. The aim is to obtain outcome data from 30 midwives and 30 pregnant women in each arm (15/cluster). In each cluster we will aim to recruit 18 midwives, 18 pregnant women (baseline), and 30 pregnant women (post-intervention follow up) to provide outcome data for statistical analysis in the pilot trial, to allow for withdrawal and loss to follow up. The aim is to obtain qualitative process evaluation data from 5 midwives in each NHS Trust in the intervention arm, and 5 pregnant women from each participating NHS Trust. We will aim to recruit 7 midwives and 10 pregnant women from each of the relevant pilot sites to allow for withdrawal and loss to follow up.

